## Abstract

**Background:**

Endoscopic retrograde cholangiopancreatography (ERCP) is an increasingly common intervention in the treatment of pancreaticobiliary disorders. Patients are often elderly with complex co-morbidities. While monitored anaesthesia care with sedation is commonly used for most cases, few would require general anaesthesia with an endotracheal tube. Both low-flow and high-flow nasal cannulas (HFNC) are established ways of delivering supplemental oxygen, but it is unclear whether one technique is better than the other. HFNC seems a promising tool for advanced procedures but evidence to support its application in high-risk ERCP cases is limited. The rate of oxygen desaturation during endoscopy has been reported to be as high as 11%–50% and the method of oxygen delivery for ERCP merits further study.

**Methods/design:**

This is a prospective, randomised, multicentre trial comparing the efficacy of oxygen supplementation through HFNC versus low-flow nasal cannula during ERCP, in a cohort of patients at risk of adverse respiratory events. A total of 132 patients will be recruited across three sites and randomly assigned to either the low-flow or the HFNC group. The primary outcome is the proportion of patients experiencing hypoxia, defined by any event of SpO2 < 90%. The secondary outcomes include parameters centred on oxygenation, requirement of airway manoeuvres, successful completion of procedure, perioperative complications, patient satisfaction and cost analysis of the consumables. An intention-to-treat principle will be applied while analysing.

**Discussion:**

The demand for ERCPs is likely to increase in the future with the aging population. Our study results may lead to improved outcomes and reduce airway-related complications in patients undergoing ERCPs. The results will be presented at national and international meetings and published in peer-reviewed journals.

**Trial registration:**

www.ANZCTR.org.au, CTRN12619000397112. Registered on 12 March 2019.

## Background

Endoscopic retrograde cholangiopancreatography (ERCP) is a common intervention in the treatment of biliary and pancreatic diseases, and the demand for ERCP is increasing. There are several difficulties for the anaesthetist to deal with. It is generally performed in a prone or lateral position under moderate to deep sedation or general anaesthesia [1–3]. In most hospitals, ERCP is usually performed outside the operating room. The patients who require this procedure are typically elderly with significant co-morbidities. General anaesthesia with an endotracheal tube may be a ‘safe option’ in the prone position in terms of having a secured airway and a lower ERCP failure rate [3]; there may be a reduction in complication rates, but intubation has drawbacks. In addition to the well-known problems associated with insertion of the tube, managing a paralysed intubated patient prone creates its own challenges. Note that there is frequently a prolongation of anaesthetic time concurrent with the use of muscle relaxants.

Deep sedation using propofol is perhaps the most commonly employed technique for ERCPs. ERCP generally requires a deeper level of sedation compared to simple gastroscopy and there is an increased risk of both partial and complete airway obstruction. The goals of deep sedation are: preserving adequate spontaneous ventilation; maintaining cardio-respiratory stability; early recovery; and minimising any hypoxaemia at all times. Hypoxemia and aspiration have occurred when these procedures have been performed under deep sedation, especially in high-risk cases [4]. Reasons for desaturation during ERCP under deep sedation have been attributed to reduced cardiopulmonary reserve, advanced age, respiratory depression, duration of the procedure, and prone positioning. The incidence of hypoxemia during any endoscopic procedure is in the range of 11%–50% [5–7] and it is possibly as high as 60% with ERCP [8] (definitions of hypoxia vary between the studies). Prolonged hypoxia is a major risk factor for periprocedural cardiac arrhythmias and myocardial ischaemia [9–11]. Any methods of avoiding such occurrences is worthy of investigation.

Regardless of the level of sedation, supplemental oxygen is regularly administered to all patients to prevent hypoxia. Conventionally, it is delivered via nasal prongs and/or an extension tubing attached to the mouth guard (the application of the endoscope in the oral cavity precludes the use of normal face masks). The recommended flow rate through the low flow nasal cannula is 2–4 L/min, while the inspired FIO_2_ (fractional inspired oxygen concentration) is dependent on the ventilatory minute volume, in the range of 0.27–0.50 [12, 13]. Patients with high American Society of Anesthesiologists (ASA) status (III) [5, 14], high body mass index (BMI) [5, 15] and those with obstructive sleep apnoea (OSA) [16] are especially at an increased risk of hypoxia during advanced endoscopic procedures such as ERCP; these patients will obtain most benefit from any improvement in oxygenation techniques. It has been the case that superior oxygen delivery options preserving spontaneous respiration without interfering with the pharyngeal cavity have been limited for these procedures.

High-flow nasal cannula (HFNC) is a new approach for improving oxygenation and ventilation that has gained popularity in procedural sedation. It has been demonstrated to provide better oxygenation compared to the venturi face mask and low-flow nasal cannula during intravenous sedation for both bronchoscopy and dental procedures [17, 18]. HFNC can provide a maximum flow up to 70 L/min and delivers a flow-dependent positive airway pressure which increases end-expiratory lung volume and thereby improves oxygenation [19]. It has numerous physiological advantages that are not possible through standard (ventilation dependent) low-flow delivery systems. These advantages include the ability to create PEEP (up to 5–7.5 cm H_2_0), reduce the work of breathing, provide constant FIO_2_ up to 100%, provide good humidification, and aid washout of the pharyngeal dead space [19, 20]. In one centre, introducing the option to use HFNC affected anaesthetic practice and decreased the usage of general anaesthesia with an endotracheal tube (for a mixed group of ERCP and endobronchial ultrasound procedures) [21]. This observational study also showed HFNC also decreased the anaesthesia only time.

High-flow nasal oxygen has been described in the critical care setting for respiratory impairment for nearly a decade [20]. It has been successfully employed in various perioperative settings such as preoxygenation and airway management, including awake intubation [22, 23]. In our own institution, we have used HFNC for endoscopy and ERCP procedures in high-risk cases and have found it convenient to use and frequently beneficial. Being administered nasally, there is nil interference with the endoscopic insertion and manipulation in the oropharynx.

The aim of the OTHER (Oxygen Therapy in High risk ERCP) trial is to assess the efficacy and safety of oxygen supplementation achieved through HFNC compared with low-flow nasal cannula during ERCP in a cohort of patients at risk of adverse respiratory events. We hypothesise that the application of high-flow nasal oxygen will reduce the incidence of major respiratory adverse events and any resulting cardiovascular problems. Measurements will be made of respiratory and haemodynamic parameters, recovery profile and patients’ satisfaction.

## Methods/design

### Study design and setting

We will conduct this prospective multicentre randomised trial as per the recommendations for interventional trials (SPIRIT, Fig. 1 and Additional file 1) [24]. The final reporting of this trial will be in accordance with the Consolidated Standards of Reporting Trials (CONSORT) statement.

**Fig. 1 Fig1:**
[figure not shown]
SPIRIT flow diagram: the schedule of enrolment, interventions and assessments. t1 is at the time of allocation and during the procedure, t2 is post anaesthesia care unit at the time of participants leaving the area and the study ends here. ASA American Society of Anaesthesiologists, BMI body mass index, OSA obstructive sleep apnoea

The OTHER trial will be conducted across three Australian hospitals: The Queen Elizabeth Hospital and Royal Adelaide Hospital, South Australia, and John Hunter Hospital, New South Wales. A total of 132 patients will be recruited. ERCP procedures are unique in terms of their presentation. A good proportion of them are undertaken as semi-urgent cases (unlike other pure electively planned cases) as inpatients and they may not get the opportunity to present to a pre-admission clinic. We are planning to recruit these patients at least 2 h before the procedure or whenever they are being assessed for anaesthesia. During this time, the patient information sheet will be provided. The recruitment and consenting are done by one of the investigators or by the anaesthetists assessing these patients. The pre-screening process would be based on the inclusion criteria mentioned below.

### Randomisation

Participants will be randomly assigned to either the low-flow nasal oxygen or the HFNC group at a ratio of 1:1 (Fig. 2). The randomisation scheme will be generated by the Clinical Trials Division of the Pharmacy Department at The Queen Elizabeth Hospital. To ensure equal distribution of the intervention arm, stratification is done in specific blocks to predetermined numbers known only to the clinical trials division. This will be revealed only at the end of the trial. The random numbers and the group assignment will be supplied in sealed envelopes and handled only by the principal investigator. A set of 25 envelopes will be dispatched and used at each site, and an additional set of envelopes will be dispatched in blocks of 20 once the first 25 are used. The envelopes will be opened just before commencing ERCP and groups are allocated to the treatment intervention. Participants and the investigators are not blinded to the allocation. The patient information sheet contains descriptions of the trial. Diagrams of HFNC as well as low-flow nasal cannula are depicted in the sheet. Further, when we commence HFNC, we are obliged to explain to the patient that they will feel a high flow of oxygen coming through their nostrils. These are the reasons why we could not blind the participants to the intervention.

**Fig. 2 Fig2:**
[figure not shown]
Study flow chart. ASA American Society of Anesthesiologists, BMI body mass index, ERCP endoscopic retrograde cholangiopancreatography, OSA obstructive sleep apnoea, PACU post-anaesthesia care unit

Data will be collected only by the investigators. The data analysts will be blinded to the intervention.

### Inclusion criteria

Adults (aged > 18 years) fulfilling any of these criteria: ASA 3 or 4; obesity (BMI > 30 kg/m^2^); obstructive sleep apnoea diagnosed either by polysomnography; being treated with CPAP for OSA; suspected OSA based on STOP BANG score >/3 (STOP BANG is an acronym for Snoring, Tiredness, Observed choking/gasping, blood Pressure elevation, BMI increase, Age, Neck size, male Gender).

### Exclusion criteria

Participants fulfilling any of the below criteria will be excluded: (1) deemed ‘difficult airway’ and/or difficult intubation based on clinical judgement and known previous difficult airway; (2) severe cardio-respiratory compromise or any other indications that necessitate the procedure to be done under general anaesthesia with endotracheal tube; (3) patients judged to be at significant risk of pulmonary aspiration. Risk assessment will be based on patient history (focusing particularly on risk factors for aspiration) and physical examination. Possible risk factors for aspiration include: increased gastric content; delayed gastric emptying; including lap band in situ; lack of fasting (< 6 h for solids and 2 h for clear fluid); increased regurgitation risk: uncontrolled or symptomatic gastro-oesophageal reflux, oesophageal strictures, Zenker diverticulum and achalasia; laryngeal incompetence due to cerebral infarct, head injuries, neuromuscular disorders (Parkinson’s disease, Gullian Barre), muscular dystrophies (cerebral palsy, cranial neuropathies); and (4) emergency surgery and any other criteria warranting general anaesthesia with an endotracheal tube.

### Intervention and comparison

Patients will be randomly allocated (computer-generated randomisation) to either the low-flow nasal oxygen group (group L; n = 66) or the high-flow nasal oxygen group (group H; n = 66). In group L, the procedure will be performed under deep sedation and analgesia, with supplemental oxygen 4 L/min via regular nasal cannula and a further supplemental oxygen source with a flow rate of 4 L/min administered through an extension tubing attached to the mouth guard. In group H, the procedure will be performed under deep sedation and analgesia similar to Group L, with oxygen delivered through a HFNC. This will be accomplished using the Optiflow THRIVE (Transnasal Humidified Rapid Insufflation Ventilatory Exchange) device (Opti-Flow, Auckland, New Zealand). Flow rate through the cannula will be commenced at 30 L/min and fractional inspired oxygen concentration will be set at 100%. The flow will be gradually increased after the administration of sedative agents and will be maintained at 50 L/min during the procedure. The flow rate may be either increased up to 70 L/min if necessary or decreased to 30 L/min if the patient does not tolerate the higher flow rate (50 L/min is very well tolerated in even very lightly sedated patients).

Standard monitoring will be applied, including continuous electrocardiogram, blood pressure automatically measured every 3 min, transcutaneous capnography and pulse oximetry. The procedures will be done in either the lateral or prone positions. A standard sedation technique will be applied for both groups. Sedation is to be provided by titrated doses of fentanyl 0.5–1.0 mcg/kg, as required, and a propofol target controlled infusion (using the Marsh model) commencing at an initial plasma target of 1.5–2.0 mcg/mL and titrated up or down during the procedure, between target values of 1–4 mcg/mL based on satisfactory depth of anaesthesia and frequency of ventilation (8–14 breaths per min). Administration of further fentanyl top up doses (25 mcg) will be at the anaesthetist’s discretion. In all cases, airway obstruction needs to be avoided.

If it is deemed necessary that during the intervention phase, if the participants’ clinical condition warrants an advanced airway such as tracheal intubation, it will be undertaken and they will be retained in an intention-to treat analysis.

### Outcome measures

#### Primary outcome

The occurrence of hypoxia, defined by any event of SpO2 (oxygen saturation measured by pulse oximetry) < 90% of any duration, will be compared between the two groups.

#### Secondary outcomes

Secondary outcomes are as follows:
Number of events of hypoxia, defined as desaturation < 90%. The mean number of events during the procedure will be compared between the two groups;Lowest recorded SpO_2_ during the procedure;Transcutaneous CO_2_. Maximum value recorded and average value during the case. The mean values during the procedure will be compared between the two groups;Lowest recorded SpO_2_% during the procedure. The mean values during the procedure will be compared between the two groups;Requirement of minor airway manoeuvres: jaw lift/jaw thrust, nasopharyngeal airway insertion. Proportion of patients requiring these manoeuvres will be compared between the two groups;Requirement of major airway manoeuvres: bag mask ventilation, endotracheal intubation. Proportion of patients requiring these manoeuvres will be compared between the two groups;Arrhythmia (any change in cardiac rhythm observed on the electrocardiogram). Proportion of patients manifesting arrhythmia during the procedure will be compared between the two groups;Total fentanyl dose. The mean values (the doses in micrograms) during the procedure will be compared between the two groups;Requirement of antispasmodic agent. Proportion of patients requiring this medication will be compared between the two groups;Total duration of procedure (starting from sedation until leaving the suite). The mean duration in minutes will be compared between the two groups;Duration under sedation/anaesthesia: measured from the time of induction till eye opening. The mean duration in minutes will be compared between the two groups;Successful completion of the procedure: Yes/No. Proportion of patients fulfilling this criterion will be compared between the two groups;Early complications – elicited as patients leave recovery;Dry mouth/nose/throat: binary outcome (constant pain or discomfort in the mouth/nose/throat). Proportion of patients experiencing this adverse event will be compared between two groups:
◦ Sensation of abdominal bloating: Y/N. Proportion of patients experiencing this adverse event will be compared between the two groups;Patients’ satisfaction score on leaving recovery: 5 points numerical rating scale:
◦ Very satisfied (5), somewhat satisfied (4), neither satisfied nor dissatisfied (3), somewhat dissatisfied (2), very dissatisfied (1). Proportion of patients at a particular threshold will be compared between the two groups;Cost analysis of the consumables: low flow versus high flow. This will be analysed for only the consumables required during the procedure for an average case and compared across the two groups. The information will be obtained from our clinical pharmacy and anaesthetic nursing department.

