### Quality control and data monitoring

The investigators and anaesthetic nursing staff will undergo special training on using and troubleshooting the transcutaneous CO_2_ equipment. Only data on respiratory, haemodynamic and perioperative outcome endpoints will be collected during the procedure and it is not time bound. Only one set of data will be collected in the post-anaesthesia care unit when they leave the area. The data will be de-identified when entered into an Excel spreadsheet for analysis. No blood or tissue samples will be collected. The original data collection will be kept for cross-checking. The data forms will be securely placed in our department’s locked filing cabinets. Any serious adverse events across any sites will be notified within 24 h to the principal investigator. Patient recruitment and data quality will be regularly checked by the investigators across the trial centres. The study involves comparing established standard practices and hence deemed as low risk to be specifically monitored by a data monitoring committee.

The electronic data will be stored in the department’s computers with password protection. After the analysis, only the principal investigator will have access to the data. A strict privacy policy will be maintained by all investigators to protect confidentiality throughout the trial process. This study will be performed in accordance with the Standard Protocol Items: Recommendations for Interventional Trials [SPIRIT] recommendations.

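### Transcutaneous CO2 and lowest SpO2 are compared as during-procedure means with no provision for a pre-intervention reading, which gives up some precision on these secondary outcomes

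*Protocol article*

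**What the plan says.** All references are to the Protocol article.

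- **Secondary outcomes, transcutaneous CO2:** "Maximum value recorded and average value during the case. The mean values during the procedure will be compared between the two groups".
- **Secondary outcomes, lowest SpO2:** the value is the lowest recorded "during the procedure. The mean values during the procedure will be compared between the two groups".
- **Statistical analysis:** continuous outcomes are summarised by mean and standard deviation, with 95% confidence intervals where appropriate. No test, model or baseline covariate is named.
- **Intervention and comparison:** "Standard monitoring will be applied, including continuous electrocardiogram, blood pressure automatically measured every 3 min, transcutaneous capnography and pulse oximetry". The section does not say when the first reading is taken or whether it is kept as data.
- **Quality control and data monitoring:** "Only data on respiratory, haemodynamic and perioperative outcome endpoints will be collected during the procedure and it is not time bound". One further set of data is taken on leaving the post-anaesthesia care unit.
- **Fig. 1 caption:** "t1 is at the time of allocation and during the procedure". This is a single combined time point. The figure itself is not available, so it cannot be checked for a baseline reading.

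**The concern.** Patients qualify through ASA 3 or 4, BMI above 30, or diagnosed or suspected sleep apnoea. Starting CO2 and SpO2 can plausibly differ between such patients for reasons unrelated to the oxygen device. When only during-procedure values are compared, that spread stays in the standard error of the arm difference. A reading taken before the intervention could remove part of it, from equipment that every patient is due to have anyway.

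The choice of covariates can wait for an analysis plan, but data capture cannot: no later plan can adjust for a value that nobody wrote down. At stake is the sharpness of three physiological comparisons in a trial with 66 patients per arm. The section on strengths and limitations lists transcutaneous CO2 measurement as a strength.

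**Working it through.** **The plan's own figure.** No standard deviation, correlation or power is given for CO2 or lowest SpO2. The only stated size is 66 per arm, for the binary primary outcome (21.4% against 5.4%, 80% power, alpha 0.05, taken here as two-sided). The unpooled formula gives (1.96 + 0.8416)² × (0.214 × 0.786 + 0.054 × 0.946) / 0.16² = 67.2, so 68 per arm. The arcsine formula gives 65. The stated size is therefore reproduced to within 2 per arm by these two formulas; the pooled formula gives 70. It matters here only as the value of n.

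**Inputs.** n = 66 per arm (Sample size calculation). r is the correlation between the pre-intervention reading and the outcome. It is an assumption, taken over 0.2 to 0.7.

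**Formulas, in units of the outcome SD.**
- Unadjusted standard error: √(2/66) = 0.174.
- Detectable difference at 80% power, unadjusted: 2.8016 × 0.1741 = 0.488.
- Adjustment for baseline multiplies the variance by 1 − r², and the standard error and detectable difference by √(1 − r²).
- Power for a 0.488 SD effect: Φ(0.488/SE − 1.96).
- Unadjusted sample size giving the same precision: 66/(1 − r²) per arm.

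| Assumed r | Variance saved | SE (SD) | Detectable difference (SD) | Power at 0.488 SD | Equivalent unadjusted n per arm |
|---|---|---|---|---|---|
| 0 (unadjusted) | 0% | 0.174 | 0.488 | 80.0% | 66 |
| 0.2 | 4% | 0.171 | 0.478 | 81.6% | 68.8 |
| 0.3 | 9% | 0.166 | 0.465 | 83.6% | 72.5 |
| 0.5 | 25% | 0.151 | 0.422 | 89.9% | 88.0 |
| 0.7 | 49% | 0.124 | 0.348 | 97.5% | 129.4 |

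These are gross gains. The small cost of estimating the covariate terms is ignored, and it matters only at the lowest correlations.

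**Chance imbalance.** If the arms differ at baseline by one standard error (0.174 SD), the unadjusted difference moves by r × 0.174: 0.035 SD at r = 0.2 and 0.122 SD at r = 0.7. The unadjusted standard error already includes this movement. It is the same cost as the lost precision and must not be counted again.

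**Which reading can serve as a baseline.** Randomisation states: "The envelopes will be opened just before commencing ERCP and groups are allocated to the treatment intervention". In the high-flow arm the cannula starts at 30 L/min with 100% oxygen, and Intervention and comparison continues: "The flow will be gradually increased after the administration of sedative agents and will be maintained at 50 L/min during the procedure". High flow therefore appears to begin before the sedatives. A reading that is merely pre-sedation may already be affected by the intervention in that arm, and adjusting for it could remove part of the treatment effect. Only a reading taken before study oxygen is safe, and one taken before the envelope is opened is cleanest.

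**The case against.** **The plan is silent rather than wrong.** The article never calls the comparison unadjusted, regression adjusted for baseline also compares means, and covariates for secondary outcomes are commonly left to an analysis plan. This stands: the article neither specifies nor excludes adjustment. What survives is the matter of data capture, because the article describes respiratory data as collected during the procedure and mentions no earlier reading. The full protocol or Fig. 1 may contain one, in which case only the analysis half of the suggestion remains.

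**A reader might infer bias.** The documents do not support that. Allocation is randomised 1:1, so the unadjusted difference is unbiased whatever the starting levels.

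**A reader might infer that an existing pre-sedation value is being discarded.** That goes too far as well. The article says that the monitors are applied, not that a baseline is recorded.

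**The spread at baseline has no figure behind it.** True. The exclusion of severe cardio-respiratory compromise requiring intubated general anaesthesia also narrows the range. Low correlations therefore belong in the calculation, and at r = 0.2 the gain is trivial. Lowest SpO2 is a minimum reached under sedation, with a baseline bounded near 100%, so a low correlation is plausible there.

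**Conclusion.** The point holds as a suggestion for improvement. As written, three secondary outcomes are compared through during-procedure values alone, and the article makes no provision for recording or using a pre-intervention reading. The cost is precision only: 4% to 49% of the variance for an assumed correlation of 0.2 to 0.7. The loss is trivial at the bottom of that range and material from about 0.5 upwards. A worthwhile gain is more likely for transcutaneous CO2 than for lowest SpO2. The primary outcome and the sample size are untouched. The size of the gain rests wholly on a correlation that the article does not give.

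**What to change.** 1. If it is not already captured, record transcutaneous CO2 and SpO2 just before the envelope is opened and before any study oxygen or sedation. This concerns data recording only and changes nothing in patient care.
2. Prespecify linear regression of maximum CO2, average CO2 and lowest SpO2 on arm, adjusted for the matching pre-intervention reading and for site.
3. For patients already enrolled, take a value from the anaesthetic record only if it clearly precedes study oxygen and sedation. Otherwise impute the overall mean of the baseline covariate, computed without regard to arm, which is acceptable for a baseline covariate in a randomised comparison.

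The cost is two extra numbers on the case form and some missing baselines among patients enrolled before the change; no new equipment is needed. Trial status reports that the trial is on hold, so the form and the analysis can be settled before recruitment resumes.

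### Total fentanyl is partly scaled to body weight but compared as an unadjusted mean in micrograms, which is valid but less precise than a weight-adjusted comparison

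*Protocol article*

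**What the plan says.** The protocol article, under Secondary outcomes, includes total fentanyl dose and states both its unit and its summary: "The mean values (the doses in micrograms) during the procedure will be compared between the two groups". It mentions neither scaling to body weight nor adjustment for it.

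Intervention and comparison describes two components of the dose. One scales with weight: "titrated doses of fentanyl 0.5–1.0 mcg/kg, as required". The other is fixed: "Administration of further fentanyl top up doses (25 mcg) will be at the" discretion of the anaesthetist. Total fentanyl is therefore a mixture of the two.

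Under Inclusion criteria, adults enter by "fulfilling any of these criteria". BMI above 30 is one, and the others are ASA 3 or 4 and diagnosed, treated or suspected sleep apnoea. Obesity is enough for entry but is not required. Under Randomisation, patients are allocated "at a ratio of 1:1", which gives 66 per arm.

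**The concern.** When a dose is given per kilogram and compared in micrograms, some of the spread between patients is simply spread in body size. A 50 kg patient would receive 25–50 mcg as a single weight-scaled dose, and a 130 kg patient 65–130 mcg. Both weights are illustrations, and any fixed top-ups would shrink the relative contrast in total dose. A cohort that admits obese patients alongside ASA 3–4 patients of any weight is likely to be spread out in this way, although the protocol gives no weight figures.

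What is at stake is precision. Variance that a known baseline measurement could explain is left in the residual, so the confidence interval for the difference in fentanyl is wider than it need be.

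**Working it through.** **Inputs from the protocol.** Weight-scaled dose 0.5–1.0 mcg/kg; top-up 25 mcg; 66 patients per arm. The protocol gives no SD, effect size or power for fentanyl, so there is no figure of its own to reproduce. The 132 belongs to the primary outcome.

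**Assumptions.** Weight W has mean 85 kg and SD s of 15 or 25 kg. One weight-scaled dose is given at a rate U, uniform on 0.5–1.0 mcg/kg and independent of W. The number of top-ups N is Poisson with mean λ = 0, 1, 2 or 3.

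**Formulas.** Total dose D = U·W + 25·N.

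- E(U) = 0.75 and Var(U) = 0.5²/12 = 0.02083, so E(U²) = 0.5625 + 0.02083 = 0.58333.
- Var(D) = 0.58333·(85² + s²) − (0.75·85)² + 25²·λ.
- Cov(D, W) = 0.75·s², so the share of variance explained by weight is R² = 0.5625·s² / Var(D).
- Narrowing of the confidence interval after adjustment = 1 − √(1 − R²).

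**One case in full** (s = 15, λ = 1). Var(D) = 0.58333·7450 − 4064.06 + 625 = 906.8. R² = 126.56 / 906.8 = 0.140. Narrowing = 1 − √0.860 = 7%.

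| Mean top-ups | R², SD 15 | Narrowing, SD 15 | R², SD 25 | Narrowing, SD 25 |
|---|---|---|---|---|
| 0 | 45% | 26% | 68% | 44% |
| 1 | 14% | 7% | 31% | 17% |
| 2 | 8% | 4% | 20% | 11% |
| 3 | 6% | 3% | 15% | 8% |

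A simulation of 400,000 doses per scenario gave the same values at SD 15. At SD 25 it gave slightly lower narrowing: 42%, 16%, 10% and 7% for zero to three top-ups. Setting the few simulated weights below 40 kg to 40 kg trims the SD a little and accounts for the difference. The lower figures are used in the conclusion.

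**In micrograms.** Take s = 20 and λ = 1. Var(D) = 0.58333·7625 − 4064.06 + 625 = 1008.9, so the SD is 31.8 mcg around a mean of 63.75 + 25 = 88.75 mcg. The 95% half-width at 66 per arm is 1.96·31.8·√(2/66) = 10.8 mcg. With R² = 225 / 1008.9 = 0.223, it falls to 10.8·√0.777 = 9.6 mcg.

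**Is mcg/kg the better scale?** A wider grid (mean weight 85 kg, weight CV 15%–30%, one or one-to-two weight-scaled doses) compares the squared CV of micrograms with that of mcg/kg. A ratio above 1 favours mcg/kg.

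- No top-ups: 1.19–3.53.
- Mean of one: 1.06–1.38.
- Mean of two: 0.95–1.16.
- Mean of three: 0.84–1.02.

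The ratios below 1 occur with a single weight-scaled dose and two or more top-ups, because 25 mcg divided by a variable weight is itself variable. Weight explains 4%–69% of the variance of raw micrograms over this grid, so adjustment reduces the residual variance in every scenario.

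**The case against.** The strongest objection is that nothing here is wrong. Absolute dose is a legitimate and readable scale, the comparison is unbiased, and a covariate for one secondary outcome is the sort of detail that often sits in an analysis plan, which is not shown. The protocol's wording does not exclude an adjusted analysis. All of this stands, and it is why the point is an improvement and not a correction. What remains is that the protocol does state the unit and the unadjusted mean, and a better comparison is available at no cost.

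The size is also open to challenge, since weights, rates and top-ups are all assumed. The larger gains need no top-ups at all, although the protocol expressly provides for them. Titration to effect could weaken the link between dose and weight further.

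A reader might infer more than the document supports:

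- **That body size biases the comparison.** It does not. Randomisation balances weight in expectation.
- **That chance imbalance in weight is a further harm.** With SD 15–25 kg and 66 per arm, the standard error of the weight difference is s·√(2/66) = 2.6–4.4 kg. The 95% chance range is about ±5.1 to ±8.5 kg, or at 0.75 mcg/kg about ±4 to ±6 mcg. The unadjusted interval already includes that noise.
- **That fentanyl is the trial's check on equal sedation.** It is the only drug dose among the listed outcomes, but the protocol never gives it that role. It relies on a common sedation technique in both arms.
- **That mcg/kg should be the outcome.** The ratios above show that this is not reliably better.

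**Conclusion.** The point holds as a minor one about precision. An unadjusted mean in micrograms is a valid comparison of a partly weight-scaled dose, but not the most precise one. With mean weight 85 kg, SD 15–25 kg, one weight-scaled dose per patient and one to two top-ups on average, weight adjustment narrows the confidence interval by about 4%–16%. The gain reaches about 42% only with no top-ups and the widest weight spread, and falls to 3%–7% with three. The direction follows from the dosing description, but the size cannot be established from the protocol. One unpowered secondary outcome is affected. No view is taken on the dosing itself.

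**What to change.** Keep total fentanyl in micrograms as the outcome. Compare the groups by linear regression of total dose on treatment group and body weight, and report the adjusted difference with its 95% confidence interval beside the unadjusted group means. Robust standard errors would be sensible, because the weight-scaled part of the dose varies more in heavier patients. Dose in mcg/kg may be shown descriptively but should not replace micrograms in the comparison.

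The cost is one sentence in the outcome definition or analysis plan and one covariate. Weight is already needed for BMI and for the weight-scaled dose, so nothing new has to be measured; it only has to be kept in the analysis file. The change should be written down before the data are compared by group.
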